#### Resistant Starch intake

##### Food records

All participants will be instructed by the APD to keep a 3-day weighed food record at Baseline (Days 1–3), Days 8–10 and Days 54–56 for assessment of mean RS intake (Supplement 6). Food records will be collected at the next study visit. Alternatively, participants can choose to log their food intake using the Research Food Diary app (Xyris Software, Queensland, Australia). To aid in the accurate measurement of food consumed, kitchen scales (Propert, China), metric measuring cups and measuring spoons will be lent to participants. Nutrient analysis of food records will be completed using FoodWorks 10 (Xyris Software, Queensland, Australia). Databases on RS content of foods are limited and RS content varies widely depending on cultivars, growing conditions, country of origin, food processing, preparation and storage methods, and methods of analysis [61]. Published RS values for individual foods vary widely. Therefore, a database created from the minimum and maximum RS values published by various authors [46, 68–70] has been created by Edith Cowan University researchers and will be utilised in this study to calculate RS intake. This database has previously been used for nutrition research [71].

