### Intervention

#### Dietary intervention

All women will receive standard GDM dietary advice in line with evidence-based guidelines [2, 40, 43, 44]. Women will be encouraged to consume a minimum carbohydrate intake of 175 g per day, from mostly low glycaemic sources, distributed across the day over three meals and three snacks. The dietary advice will promote a low saturated fat intake and higher consumption of vegetables, fruit, dairy and whole grains.

After Baseline data are collected, women who are randomised to either of the two dietary intervention groups (RS Diet & RS Supp) will receive additional dietary education on consuming a high RS diet commencing on Day 3. All RS dietary education will be conducted by the PI who is an experienced Accredited Practising Dietitian (APD). A standardised teaching plan (Supplement 3) and education materials will be utilised (Supplements 4 & 5). Participants will be provided with written material including a Gut Feeling cookbook [45] and sample menus, as well as some non-perishable samples of high RS foods to allow for immediate adoption of the diet. Dietary RS will be measured at Baseline, Day 10 and Day 56 using 3-day weighed food records (Supplement 6). Evidence of compliance with the high RS diet will also be monitored via urine samples for metabolomic analysis and change in stool microbiota at the same timepoints. Participants will be asked to continue the high RS diet until the delivery of their child.

The RS education tools and strategies have been piloted in a non-pregnant population and achieved a median increase in dietary RS intake of ≥6.6 g RS per day (unpublished data). The typical intake of RS in Australian women aged 19–44 years has been estimated to range from 2.9–8.3 g per day [46]. Similarly, recent data from the United States estimated the mean daily intake of RS to be 1.9 g per 1000 kcal for women of this age [47], which would equate to 3.8–5.7 g per day.

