#### RS supplement

The RS Supp group will consume an RS supplement of high-amylose maize (HAMS) type 2 resistant starch. Participants will be given a 600 g tub of HAMS each fortnight, along with a 40 ml scoop. They will be instructed and provided with written material (Supplement 7) on how to prepare and incorporate the RS supplement into cool fluids or foods in their diet. As with all low-digestible carbohydrates, gastrointestinal (GI) discomfort is a known side effect of rapid introduction of RS, therefore, participants will introduce HAMS over a two-day adjustment period. They will be instructed to consume 1 scoop (20 g) per day for 2 days, taking half in the morning and the rest at night. Then, increasing to a dose of 1 scoop (20 g) morning and night for the remainder of their pregnancy. The RS supplement contains 40% RS type 2. The final amount of RS in the 40 g of HAMS per day will be 16 g, which is below the level of 45 g per day of RS supplementation that is known to be tolerated with minimal side effects, most of which are flatulence [48]. Intakes of up to 80 g RS per day have been tolerated without diarrhoea [48]. Those in the high RS diet plus RS supplement are unlikely to achieve this amount. Consumption and compliance of the RS supplement will be monitored by weight of unconsumed HAMS returned fortnightly. Participants will use a daily RS supplement diary to record intake as an additional measure of compliance. We have shown in a recent 2-week feasibility study, 100% compliance with consumption of the RS supplement and minimal GI side effects in 10 female participants with prediabetes or T2DM (unpublished). GI tolerance of the supplement will be measured via a daily bowel symptom diary for the first 10 days and Days 47 to 56.

Participants can withdraw from the study at any time for any reason. Participants will be withdrawn by the investigator if they commence antibiotics, steroids, metformin or if they can no longer comply with the study’s schedule of assessments (Table 1).

**Table 1 Tab1:** Participant measurements and collection summary

	Day 1	Day 3	Day 10	Day 28	Day 42	Day 56	Day 7 post-partum
Recruitment & consent	√						
Randomisation of subjects	√						
Attend clinic	√	√	√		√	√	
Self-monitoring blood glucose data collection		√	√			√	
FreeStyle Libre Pro application	√				√		
Questionnaires:							
medical Hx	√						
medication	√						
GI symptoms	√		√			√	
Quality of Life SF36	√		√			√	
Weight measured	√		√			√	

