3-day weighed food records collected		√	√			√	
Bowel symptoms, RS supplement, medication & exercise diary collected		√	√			√	
H_2_ breath test		√	√			√	
Fasting Bloods			√			√	
Maternal stool samples		√	√			√	√
Neonatal stool sample							√
Maternal urine sample		√	√			√	
Neonatal urine sample							√
Breastmilk sample							√
Study instructions and materials							
RS diet education		√					
supplement regime if applicable		√					
Reminder phone call or text				√			
Assessment of Medical Records for							√
adverse outcomes							
delivery method							
birth weight, length							
feeding method							
NICU admission							
length of stay							

*Note: RS* Resistant starch, *NICU* Neonatal Intensive Care Unit

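### The baseline food record (Days 1–3) overlaps the Day 3 start of the RS intervention, so three complete pre-intervention days of RS intake cannot be obtained

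*Protocol article*

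**What the plan says.** Under Food records, all participants are to "keep a 3-day weighed food record at Baseline (Days 1–3", with further records on Days 8–10 and 54–56, to assess mean RS intake. The same section says "Food records will be collected at the next study visit".

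Under Dietary intervention, one sentence gives both the order and the day. It opens "After Baseline data are collected, women who are randomised to either of the two dietary intervention groups" and goes on to promise those women "additional dietary education on consuming a high RS diet commencing on Day 3".

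Table 1 ticks the row "3-day weighed food records collected" at Days 3, 10 and 56. It ticks RS diet education and "supplement regime if applicable" at Day 3. Clinic attendance is ticked at Days 1, 3, 10, 42 and 56, with none after Day 56. Fasting bloods are ticked at Days 10 and 56.

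On the lead-in to the supplement, the RS supplement section says: "They will be instructed to consume 1 scoop (20 g) per day for 2 days". Supplement intake is also tracked outside the food record, by a daily diary and by the weight of returned product.

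Elsewhere the article takes only the first two days as baseline: for the bowel symptom scores (Bowel symptoms record), and for self-monitored glucose and post-prandial excursions (Statistical analyses).

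**The concern.** Day 3 carries two labels: last day of the baseline diet record and first day of the RS intervention. The article does not say when recording on Day 3 stops, and neither possible answer gives three full usual-care days.

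The food record is the only instrument that expresses dietary RS in grams. Urine metabolomics, stool microbiota and breath hydrogen are indirect, and breath hydrogen is not yet funded. The Discussion presents the question of whole foods alone versus a supplement as a distinctive feature of the study, and accepts that not providing food may limit compliance. A null glycaemic result in the RS Diet arm would be hard to interpret without a sound estimate of how far RS intake rose. A part-day counted as a whole day, or an intervention day counted as baseline, would distort that estimate.

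**Working it through.** The plan states no figure for this point, so there is none to reproduce. The check sets out the two ways Day 3 can be handled and bounds the error in each.

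**Inputs from the protocol article**
- Record length: 3 days (Food records).
- Expected rise in dietary RS: at least 6.6 g/day, a pilot median in non-pregnant people (Dietary intervention).
- Supplement on its first two days: 20 g/day at 40% RS = 8 g RS/day. Full regimen: 16 g RS/day (RS supplement).

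**Assumptions, with no value in the documents**
- *s*: share of the visit day's RS already recorded when the record is handed in. Illustrated at 0.2–0.3.
- *f*: share of Day 3 both eaten on the intervention and still entered in the baseline record. Range 0 to 1.
- The mean is taken over three days. The article says only that mean intake is assessed and fixes no divisor.

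**Case A: the record closes at the Day 3 visit**

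No intervention food enters the record, so inflation is 0. Day 3 is a part-day in all three arms.

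Understatement of the mean = 1 − (2 + *s*)/3
- *s* = 0.2: 1 − 2.2/3 = 27%
- *s* = 0.3: 1 − 2.3/3 = 23%

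The records for Days 8–10 and 54–56 are collected on Days 10 and 56, so they are cut off in the same way. Fasting bloods are drawn on both days, so little may have been eaten before the visit. If *s* is the same at each time point, the measured rise shrinks in the same proportion:
- 6.6 × 2.2/3 = 4.8 g
- 6.6 × 2.3/3 = 5.1 g

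**Case B: recording continues after education on Day 3**

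Baseline is raised in the RS arms only.

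Inflation in RS Diet = *f* × 6.6/3

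| *f* | Added to baseline (g/day) | A 6.6 g rise reads as (g) | Understated by |
|---|---|---|---|
| 0 | 0 | 6.6 | 0% |
| 1/3 | 0.73 | 5.87 | 11% |
| 2/3 | 1.47 | 5.13 | 22% |
| 1 (ceiling) | 2.2 | 4.4 | 33% |

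For RS Supp the dietary part is the same. Only if supplement RS is also counted in the food record does more enter. The ceiling is then (6.6 + 8)/3 = 4.9 g/day, and a rise of 6.6 + 16 = 22.6 g reads as 17.7 g (about 22% too small).

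**With baseline limited to Days 1–2**, both errors at baseline are zero.

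**The case against.** A reader might infer that baseline RS intake is inflated in the two RS arms and the achieved rise therefore understated. The documents do not establish this. The Dietary intervention section places RS education after baseline data collection, and Table 1 has the record collected at the same Day 3 visit. In that order no intervention intake enters the record and inflation is exactly zero.

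The ceilings in Case B are also unlikely to be reached. Education takes place at a visit during Day 3, so food eaten earlier that day is not intervention food and *f* falls below 1. The first-day supplement is split between morning and night. If the visit follows the morning portion, at most half of the 8 g RS, 4 g, falls on Day 3. Because the supplement has its own diary and returned-weight check, it may never be counted in the food record.

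The Case A percentages rest on an assumed share and an assumed divisor. The record instructions are in a supplement that is not shown, and app logging might allow a day to be completed after the visit.

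Finally, whether the arms separated can be read directly from the randomised comparison of intake at Days 8–10 and 54–56, which needs no baseline. A Day 3 overlap does not bias it.

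These objections stand, and they limit the point to a timing conflict of uncertain size. They do not remove it: the stated three-day window still cannot be filled with complete pre-intervention days. The rule of collection at the next visit does not settle when Day 3 recording ends. For the last record, Table 1 shows no clinic attendance after Day 56 at which a completed Day 56 could be returned.

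**Conclusion.** The point holds as a scheduling conflict. The protocol fixes a three-day baseline record whose third day is also the day of record collection, RS education and the start of the intervention.

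Under the order the text implies, the result is a part-day in all arms. A three-day mean would be about 23–27% too low if 20–30% of the day's RS is recorded and the divisor is three. Under continued recording, baseline is raised in the RS arms only, by between 0 and 2.2 g/day in RS Diet. The 33% understatement at that ceiling is a bound, not an estimate. Any further inflation in RS Supp depends on supplement RS being counted in the food record.

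What is at risk is change from baseline in a secondary adherence measure. The Day 3 overlap does not affect the primary fasting glucose outcome or the between-arm comparison of intake at follow-up.

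**What to change.** - In all three arms, compute baseline RS intake only from complete days before RS education, that is Days 1–2. This matches the two-day baselines already used for bowel symptoms and self-monitored glucose.
- Average every food record, including those around Days 10 and 56, over the complete days recorded, not over a fixed three.
- Reconcile Dietary intervention, Food records and Table 1 so that they state when the baseline record closes relative to RS education.

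Moving the later records to Days 7–9 and 53–55, so that they end before the visit, is optional. It would give three complete days but would separate the diet record from the bowel diary and post-prandial glucose windows, which both run on Days 8–10 and 54–56.

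The cost is about one sentence in the protocol and a matching line in the record instructions. The downside is a slightly noisier mean, based on about two days instead of three.

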##### RS supplement consumption diary

Participants will be provided with a supplement diary as one measure of compliance with the RS regime (Supplement 13). Compliance with the study protocol will be achieved if at least 80% of the RS supplement doses have been recorded as consumed over the study period.

##### RS supplement returned

Weighed portions of the RS supplement will be provided to participants fortnightly. Unconsumed RS supplement will be returned by participants and weighed on kitchen scales (Propert, China), to assess the percentage consumed and subsequent compliance with the RS consumption target.

##### Breath H_2_

A handheld hydrogen breath analyser ([name] Diagnostics Ltd., UK) will be used to assess change in H_2_ production with the RS interventions. This will also be used as a measure of compliance with the RS diet and RS supplement. Breath H_2_ measurements will be taken Day 3, Day 10 and Day 56. Ethics approval has been obtained to collect Breath H_2_ data, however, funding has to be secured.

#### Health-related quality of life

Participants will complete the RAND 36-Item Health Survey 1.0 (*SF-36*) [72] at Baseline and Day 10 and Day 56. Scoring will be completed and standardised with Australian reference ranges using the methods and data from the Australian Longitudinal Study of Women’s Health [73]. Scores will determine if the health-related quality of life is maintained across nine health domains during the intervention.

#### Metabolomics

##### Blood (maternal)

Fasting maternal blood samples will be collected on Day 10 and Day 56. Phlebotomy and processing will be performed by a registered pathology service following their standard operating procedures for handling blood. In addition to a fasting glucose test, 8.5 ml of blood will be drawn into a serum tube, centrifuged, 1 ml aliquots transferred into 4 tubes and stored in a − 80 °C freezer for analysis of SCFA content, lipids and metabolomics.

##### Urine (maternal and neonatal)

First void maternal urine samples will be collected as per a standard procedure (Supplement 14) at Baseline, Day 10 and Day 56 and stored at − 80 °C until metabolomic analysis can be performed at the Australian National Phenome Centre, Western Australia. Urinary metabolomic markers of foods consumed will be used to assess compliance with the consumption of high RS foods by the RS intervention groups. Additionally, metabolomic analysis will seek to identify additional biochemical markers that enable a better understanding of the systems biology effects of the intervention.

A neonatal urine sample for metabolomic analysis will be collected by the mother 1-week post-partum as per a standard procedure that will be provided with the stool sample kits before discharge (Supplement 15).

#### Maternal and neonatal outcomes and cost of antenatal care

Maternal and neonatal outcomes data will be collected from the DMR after discharge. Diagnosis Related Group (DRG) [74] data will be collected for calculation of hospital costs. Maternal outcome data collection will include the number of ANC clinic visits, Maternal Foetal Assessment Unit visits, antenatal admissions, delivery method, post-partum maternal length of stay, and feeding method on discharge.

After discharge, data on admission to the Neonatal Intensive Care Unit (NICU), reason for admission and length of stay will be collected from the DMR of the infant to determine the frequency of admissions to NICU in the intervention groups compared to the control group. NICU admission for neonatal hypoglycaemia or respiratory support is a known complication in babies of GDM mothers and is one of our secondary outcomes for the study. There is a linear relationship between glycaemia and admissions to NICU in offspring of women with GDM [6]. We will record this outcome and collect neonatal samples as and when the baby’s clinical condition allows. We accept that research on pregnant women raises particular safety concerns. It is noteworthy that our intervention is safe and we do not expect serious adverse events as a direct result of the intervention. We expect neonatal deaths to be not different from the general population.

### Data management

Individually identifiable data will be coded as soon as possible. Data and codes will be kept in separate lockable filing cabinets within a swipe card accessible office and access to the data will be restricted to the research team. Electronic data will be kept in a de-identified format and stored on a password-protected computer or secure server and for a minimum of 25 years. At the end of the retention period, data files and any hard copy source data will be deleted/shredded as per the South Metropolitan Health Service and Edith Cowan University data management requirements. Data collected on participants who later withdraw will be used in analysis if required unless consent to use it has been withdrawn.

The trial investigators/institutions will permit trial-related monitoring, audits, and regulatory inspections, providing direct access to source data/documents. This may include, but not limited to, review by Human Research Ethics Committees and institutional governance review bodies.

### Statistical analyses

Baseline demographic and outcome variables will be described and compared for differences between groups. Continuous variables will be described as mean ± standard deviation (SD) and nominal and ordinal variables as frequencies and proportions. All continuous variables will be examined for normality using the Shapiro-Wilk test. Descriptive statistics for non-normal continuous variables will be presented as median ± interquartile range (IQR).

FBG and PPBG will be monitored on the first 2 days and averaged to provide a Baseline measure of each outcome. These will be compared to those measured over the subsequent 8 days, and then again between Days 48 and 56, across the three dietary groups (Control, RS Diet and RS Supp) using linear mixed modelling with group-by-time interaction. Analysis will assess if a 0.3 mmol/L reduction is achieved. Demographic variables such as age, pre-pregnancy BMI, parity and ethnicity will be adjusted in the model. Statistical analyses will be performed using SPSS® (Statistical Package for Social Sciences, version 27 for Windows).

The number of PPBG excursions experienced by a participant per day between Days 4 to 10 will be examined and compared relative to the number determined at their Baseline over the first 2 days of the usual care diet. Generalised Mixed Modelling will be utilised to assess whether a dietary change reduces the frequency of PPBG excursions as compared with norm with adjustments for relevant demographic variables.

Different R packages and PRIMER 7 (Quest Research, NZ), a non-parametric statistical software package, will be used to assess change within and between groups for microbial composition. Distance Based Linear Modelling (DistLM) will be used to look for a correlation between change in stool microbiota or SCFA & measures of glycaemia.

Direct and indirect costs savings related to any reduction in insulin treatment or improvements in maternal and neonatal outcomes will be calculated from DRG codes, Weighted Activity Units (WAU) and the National Efficient Price (NEP) and reported [74].

Missing data will be treated in statistical analysis as missing and coded as 999 or left blank, so as not to affect the accuracy of the analysis. Prior to any statistical analysis, all data will be explored for outliers. Any outliers found will be cross-checked with the source file. Any true outliers will be checked with the clinician before being removed/left in the dataset.

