### Sample size

In a study by Asemi et al. [42], the average woman with GDM has a mean FBG of 5.175 ± 0.86 mmol/L. In RS supplementation trials, a difference in FBG as large as 0.4 mmol/L has been observed between control and RS supplemented groups [38]. This study aims to demonstrate a reduction in FBG of 0.3 mmol/L, which corresponds to a small to medium Cohen’s effect size (*d* = 0.35). Based on a repeated-measures design with three groups (Control, RS Diet, RS Supp) and three time points (Baseline, Day 10 and approximately Day 56), a minimum sample size of 69 (i.e., 23 per group) is required to detect a small to medium within-between interaction effect (Cohen’s *f* = 0.175) at 80% power and 5% level of significance. Allowing for an attrition rate of around 30%, the final total sample size required is 90 (i.e., 30 per group). Women who commence insulin therapy will remain in the study.

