### Primary outcome

#### Fasting blood glucose

The primary outcome of this study will be a reduction in median FBG from Baseline, within and between groups. Baseline FBG will be recorded from the diagnostic OGTT results [41]. Subsequent venous blood samples will be collected after an overnight fast at Day 10 and Day 56 and analysed for FBG following protocols from the National Association of Testing Laboratories. FBG within treatment targets (< 5.1 mmol/L) [49] is the measure of glycaemic control that has been most difficult to achieve with standard GDM diet and lifestyle interventions and therefore the variable most likely to indicate the need for medical therapy, such as insulin [50]. If FBGL below 5.1 mmol/L is not achieved by Day 10, insulin therapy will commence. Participants treated with insulin will remain in the study.

Routinely women will receive self-monitoring of blood glucose (SMBG) education. Participants will be provided with an SMBG meter and instructed on measuring blood glucose levels four times daily (FBG and 2-h post-prandially). The SMBG meters used will be either Contour Next (Ascensia Diabetes Care, Switzerland), Accu-Chek Guide (Roche Diabetes Care, Switzerland) or One Touch Verio (LifeScan, USA) and meet International Organization for Standardization (ISO) standards for accuracy. Data from these models will be uploaded via the Diasend Uploader (Glooko, USA). FBG will be monitored on the first 2 days and averaged to provide a Baseline measure. This will be compared to the moving averages over the subsequent 8 days of testing, and then again between Days 48 and 56, across the three dietary groups (Control, RS Diet and RS Supp) using mixed model ANOVA with group-by-time interaction.

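### The primary fasting glucose outcome is defined twice, with conflicting baselines and windows, and the 0.3 mmol/L target sits with the version that was not sized

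*Protocol article*

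**What the plan says.** The Fasting blood glucose section, under Primary outcome, opens with this definition: "The primary outcome of this study will be a reduction in median FBG from Baseline, within and between groups". It then fixes the data source: "Baseline FBG will be recorded from the diagnostic OGTT results", and "Subsequent venous blood samples will be collected after an overnight fast at Day 10 and Day 56 and analysed for FBG".

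Three other places agree with that laboratory schedule. The Abstract (Methods) lists fasting plasma glucose at Baseline, Day 10 and Day 56. Table 1 and the Metabolomics section place fasting bloods at Day 10 and Day 56. The Sample size section plans for 0.3 mmol/L on "three time points (Baseline, Day 10 and approximately Day 56".

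The second paragraph under the same Primary outcome heading brings in meter readings and gives them their own baseline: "FBG will be monitored on the first 2 days and averaged to provide a Baseline measure". They are compared with moving averages over the next 8 days, and again over Days 48 to 56, by a mixed model with a group-by-time interaction.

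The Statistical analyses section has one FBG model. Its baseline is again a 2-day average ("FBG and PPBG will be monitored on the first 2 days and averaged to provide a Baseline measure of each outcome"), followed by the next 8 days and Days 48 to 56. Directly after the model comes the criterion: "Analysis will assess if a 0.3 mmol/L reduction is achieved". The section does not mention the OGTT baseline or the venous samples.

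**The concern.** The two versions of FBG differ in instrument, baseline and averaging. One baseline is the diagnostic test that precedes enrolment. The other is taken on the first 2 study days, which the Statistical analyses section describes as days on the usual care diet. One follow-up value is a single laboratory sample, the other an average over many days of home readings.

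Followed as written, the 0.3 mmol/L criterion is read from a measure other than the one first declared and sized. Neither participants nor investigators are blinded (Randomisation section), and both FBG results can claim to be primary because neither is ranked above the other. The choice between them can then be made after the results are known.

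**Working it through.** **1. The definitions side by side**

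| Place in the protocol | Baseline | Follow-up | 0.3 mmol/L attached? |
|---|---|---|---|
| Fasting blood glucose, paragraph 1 | OGTT value | Venous, Day 10 and Day 56 | No |
| Sample size | Baseline visit | Day 10, about Day 56 | Yes (planning target) |
| Fasting blood glucose, paragraph 2 | Mean of first 2 days (meter) | Next 8 days; Days 48–56 | No |
| Statistical analyses | Mean of first 2 days | Next 8 days; Days 48–56 | Yes (analysis criterion) |

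The Statistical analyses section does not name the meter. That it means meter data is an inference from two facts. The windows match paragraph 2 and cannot be filled by one OGTT value and two venous draws. It also handles FBG together with post-prandial glucose, which the Secondary outcomes section says is self-monitored.

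**2. What was sized**

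Inputs from the Sample size section: 0.3 mmol/L, SD 0.86, three groups, three time points, 5% level. Effect size: 0.3/0.86 = 0.349, and half of that is 0.174, matching the stated d = 0.35 and f = 0.175. For the within-between interaction, λ = f²·N·m/(1−ρ). With N = 69, m = 3 and an assumed ρ = 0.5, λ = 0.030625 × 69 × 3/0.5 = 12.68 on 4 and 132 degrees of freedom, giving power 0.811. N = 69 is the smallest multiple of 3 that reaches 80%, so the stated figure reproduces. It describes a three-visit design, which the laboratory schedule fits and the meter windows do not.

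**3. Precision of the two measures**

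Assumptions: 0.86 is the SD of a single reading for either measure, within-woman correlation is 0.5, day-to-day noise is independent, response does not vary between women, there are 23 per arm, and one RS arm is compared with Control. Variance is 0.86² = 0.74, split into 0.37 between and 0.37 within women.

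- Venous, one reading minus one reading: variance of change 0.37 × 2 = 0.74; SE = √(2 × 0.74/23) = 0.25.
- Self-monitored, 8-day mean minus 2-day mean: variance of change 0.37 × (1/8 + 1/2) = 0.231; SE = √(2 × 0.231/23) = 0.14.

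**4. Consequence of leaving both open**

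Let r be the correlation between the two estimates of the same contrast.

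- No true effect, either test at 5% may support the claim: for r = 0, 1 − 0.95² = 9.75%. For r > 0, the probability that at least one of two correlated normal statistics exceeds 1.96 in absolute value was simulated.
- True effect exactly 0.3 on both measures: each estimate reaches 0.3 half the time, and the two disagree with probability arccos(r)/π.

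| r | At least one false positive | Disagree on reaching 0.3 |
|---|---|---|
| 0 | 9.75% | 50% |
| 0.3 | 9.5% | 40% |
| 0.5 | 9.1% | 33% |
| 0.7 | 8.4% | 25% |
| 0.9 | 7.0% | 14% |

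**The case against.** The best defence is that a venous model is already signalled. The Abstract says mixed model analysis of variance will assess change in glycaemia, and the Sample size section describes a group-by-time interaction over three visits; the detail may sit in an analysis plan that is not shown. A reader might therefore go too far in inferring that the declared endpoint has no analysis at all. That part of the defence stands. It does not remove the conflict, because the Statistical analyses section goes beyond omitting detail: it fixes a different baseline and different windows and puts the criterion on them.

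A reader might also infer that the trial tests something outside its declared primary outcome. The text does not support that either, since self-monitored FBG sits under the Primary outcome heading. The accurate charge is double definition.

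Three further inferences are tempting and not supported:

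- Sensor FBG is not a third contender. It falls under Secondary outcomes and is subject to funding.
- Meter values are not simply reported by unblinded women. Data are uploaded electronically from the device, although participants still control when they test.
- The early window need not dilute the effect by half. That requires a linear build-up and one flat 8-day mean, whereas the protocol speaks of moving averages.

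On size, both measures come from the same women, so correlations near zero are a worst case and the upper ends of the ranges should be read as ceilings. The protocol does not say that 0.86 is a single-reading SD. The figures concern one pairwise contrast, while the planned test is an interaction.

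**Conclusion.** The point holds as an internal contradiction: two primary FBG measures with conflicting baselines and windows, and a 0.3 mmol/L target sized on the three-visit schedule but assessed on the multi-day windows. This follows from the text and does not depend on the calculations. Under the stated assumptions, the cost of leaving it unresolved is a false-positive rate of about 7% to 10% for one contrast if either result may carry the claim. With a true effect of exactly 0.3, the two measures would disagree on reaching 0.3 in about 14% to 50% of trials. The lower end of each range applies at a correlation of 0.9 and the upper end at 0. The sample size calculation is not in dispute on this point. A related mismatch should be settled with it: the outcome is declared as a change in median, but a linear mixed model estimates means.

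**What to change.** Amend the Fasting blood glucose and Statistical analyses sections, before outcome data are examined, as follows:

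- Name venous FBG as the sole primary measure, with the OGTT value as Baseline and follow-up at Day 10 and Day 56.
- Fit the linear mixed model with group-by-time interaction, already stated, to those three visits.
- Express the primary outcome as a change in mean, to match that model.
- Read the 0.3 mmol/L target only from named between-arm venous contrasts: each RS arm versus Control at a stated visit.
- Label self-monitored FBG, with its own baseline and windows, as a supportive secondary analysis that cannot replace the primary. Sensor FBG is already secondary and needs no change.

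The cost is wording in two sections. No new data are needed, and the change does not alter N, because this is the three-visit design that was sized (69 at ρ = 0.5). The downside is small: a single venous value is noisier than a multi-day self-monitored mean (SE about 0.25 versus 0.14 under the assumptions above). The self-monitored result remains available as support.
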